### Statistical analysis

All statistical analyses will be performed using SPSS 17.0 statistics software. For quantitative data, the distribution pattern and homogeneity of variance will be examined. If there is a symmetric distribution, the mean (M) ± standard deviation will be used for statistical description, otherwise the M interquartile range (IQR) will be used to describe the trend of concentration and amount of scatter. If this condition is met, the Student's t-test will be used to compare the differences between the quantitative indices between the groups, otherwise the Wilcoxon rank-sum test will be used. For categorical data (binary classification and multiple classification), the composition ratio will be used for statistical description. Based on the observation of a theoretical frequency distribution, the χ^2^ or Fisher's exact test will be used, depending on the specific situation. The ranked data will be analyzed using the Wilcoxon rank-sum test.

Primary and secondary outcomes will be analyzed by the superiority test in accordance with the principle of intention-to-treat, using Per Protocol Set (PPS) and Full Analysis Set (FAS) datasets. The indices of safety evaluation will be analyzed using the Save Set (SS) dataset. The significance level in this study will be set at α = 0.05, and the one-sided test will be used. The detailed statistical analytical methods for primary and secondary outcomes and baseline data are shown in Table 
2 (variables, measures, and methods of analysis).

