### Sample size and statistical analysis

#### Sample size

Based on the myopia diopter described in the literature
[27], the sample size will be estimated using the formula for superiority test sample size for two quantitative samples
[28]. The inspection significance level α = 0.05 (two-sided) with a combined standard deviation (S) of 0.25, will be obtained according to the literature, where *u*_1*-α*_, *u*_1-β_ are the bounds of the one-sided standard normal deviation, *u*_1–0.05_ = 1.645, and *u*_1-o.20_ = 0.845. *δ*_u_ is the effective boundary (*δ*_u_ >0), assuming *δ*_u_ = 0.2; θ is the estimate of the overall mean difference value of the acupuncture and control groups, and will be set at 3.0 according to the literature
[27]. By substitution into the above formula with n = 79 and an expected dropout rate of 20%, a total of 100 cases will be included. The sample ratio between the groups will be 1:1.

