**Table 2 Tab2:** **Variables, measures, and methods of analysis**

Variable/outcome	Hypothesis	Outcome measure	Methods of analysis
1) Primary	Intervention improved outcome from baseline to 7 days	Adherence% (>80%) [binary]	
Diopter	Diopter reduced or increased after treatment	Diopter [continuous]	t-test (rank-sum test) or repeated measurement
2) Secondary	Intervention improved outcome from baseline to 7 days	Adherence% (>80%) [binary]	
Visual acuity	Visual acuity did not increase or decrease after treatment	Visual acuity changes [continuous]	t-test (rank-sum test) or repeated measurement
Axial length	Axial length was not increased	Axial length changes [continuous]	t-test (rank-sum test) or repeated measurement
Lens thickness	Lens thickness was not increased	Lens thickness changes [continuous]	t-test (rank-sum test) or repeated measurement
Ciliary body thickness	Ciliary body thickness was not increased	Ciliary body thickness changes [continuous]	t-test (rank-sum test) or repeated measurement
Eye symptoms and systemic symptoms	No adverse symptoms	No adverse symptoms	Chi-squared test or Fisher’s exact test
Compliance	Compliance	Cure rate [binary]	Chi-squared test or Fisher’s exact test
Combination therapy/treatment	Improvement occurred	Whether other drugs were used during treatment [binary]	Chi-squared test or Fisher’s exact test
Adverse event	Improvement occurred	Presence of drug-related adverse event [binary]	Chi-squared test or Fisher’s exact test
3) Baseline analyses:		Adherence% (>80%) [continuous]	
Age		CRF [continuous]	t-test (rank-sum test)
Weight and height		CRF [continuous]	t-test (rank-sum test)
Female versus male		CRF [binary]	Chi-squared test or Fisher’s exact test
Race		CRF [more categories]	Chi-squared test or rank-sum test
Birth weight		CRF [continuous]	t-test (rank-sum test)
Preterm children		CRF [binary]	Chi-squared test or Fisher’s exact test
Parental myopia or not		CRF [binary]	Chi-squared test or Fisher’s exact test
Sibling myopia or not		CRF [binary]	Chi-squared test or Fisher’s exact test
Daily close reading time		CRF [continuous]	t-test (rank-sum test)
Outdoor time		CRF [continuous]	t-test (rank-sum test)
Eye exercises every day or not		CRF [binary]	Chi-squared test or Fisher’s exact test
Daily sleep time		CRF [continuous]	t-test (rank-sum test)
Room light conditions		CRF [binary]	Chi-squared test or Fisher’s exact test
Poor reading habits		CRF [more categories]	Chi-squared test or rank-sum test

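### The significance level is labelled 0.05 two-sided in the sample-size section, but both the calculation and the planned test use one-sided 0.05

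*Protocol article*

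**What the plan says.** The Sample size section opens its inputs with "The inspection significance level α = 0.05 (two-sided) with a combined standard deviation (S) of 0.25". The same sentence goes on to say that the two normal quantiles "are the bounds of the one-sided standard normal deviation, *u*_1–0.05_ = 1.645", with 0.845 for 80% power. It adds a superiority margin (δ_u "is the effective boundary (*δ*_u_ >0), assuming *δ*_u_ = 0.2") and a mean difference θ that "will be set at 3.0 according to the literature". The stated result is n = 79, raised to 100 in total for 20% dropout.

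The Statistical analysis section says that primary and secondary outcomes are analysed by a superiority test, names Student's t-test or the Wilcoxon rank-sum test, and fixes the threshold: "The significance level in this study will be set at α = 0.05, and the one-sided test will be used". It does not mention the 0.2 margin.

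Table 2 words the hypothesis for the primary outcome as "Diopter reduced or increased after treatment".

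**The concern.** A two-sided 0.05 level and a one-sided 0.05 test are different decision rules. The first puts 2.5% in the tail that favours acupuncture, the second 5%. With both in print, a reader cannot tell which rule decides the primary outcome, and the choice could be made after the data are seen. The article gives no reason for one-sided testing.

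The threshold matters more than usual here. There is no sham control, so children and guardians know the allocation, and the refraction procedure includes subjective steps. Any bias from this is likely to favour acupuncture, the same direction in which the one-sided rule is more lenient.

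**Working it through.** **Inputs.** From the Sample size section: SD 0.25, margin 0.2, quantiles 1.645 and 0.845, θ = 3.0, n = 79, dropout 20%. From Study design: 50 per group, so 50 × 0.8 = 40 evaluable per group. The two-sided 0.05 quantile is 1.960.

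**1. The plan's own figure.** The usual formula per group is n = 2(u_α + u_β)² S² / (θ − δ_u)².
- With θ = 3.0: 2 × (1.645 + 0.845)² × 0.0625 / 2.8² = 0.10, and with 1.96 it is 0.13. Either rounds up to one child per group, so n = 79 does not reproduce.
- With θ assumed to be 0.3: 2 × 2.490² × 0.0625 / 0.1² = 77.5, so 78 per group, close to 79.
- Same assumption with 1.96: 2 × 2.805² × 0.0625 / 0.01 = 98.4, so 99 per group. The ratio 98.35 / 77.50 is 1.27.

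The figure of 79 therefore fits one-sided 0.05 and does not fit two-sided 0.05. The value 0.3 is an assumption that nearly recovers the plan's number; the article does not state it. The 78 is a per-group number, whereas the article reaches 100 in total from 79 / 0.8 = 98.75. That mismatch and the value of θ are separate matters.

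**2. If the test is against zero.**
- Error in acupuncture's favour: 1 − Φ(1.645) = 0.050 under the one-sided rule and 1 − Φ(1.960) = 0.025 under two-sided 0.05.
- A favourable result with a two-sided p between 0.05 and 0.10 is positive under the first rule and not under the second.
- Standard error with 40 per group: 0.25 × √(2/40) = 0.0559. For an assumed θ of 0.3 the noncentrality is 0.3 / 0.0559 = 5.37. Power (noncentral t, 78 degrees of freedom) is above 99.9% under either rule.

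**3. If the 0.2 margin is tested.**
- One-sided 0.05 needs an observed difference of about 0.2 + 1.665 × 0.0559 = 0.293 D. The 5% (or 2.5%) error then applies at a true difference of exactly 0.2 D. At no difference, the chance of success is about 1 in 10 million (normal approximation).
- For an assumed θ of 0.3 the effect beyond the margin is 0.1 and the noncentrality is 0.1 / 0.0559 = 1.79. Power with 40 per group is 55.1% at one-sided 0.05 and 42.3% at one-sided 0.025.

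| | Against zero | Against the 0.2 margin |
|---|---|---|
| True difference at which 5% vs 2.5% applies | 0 | 0.2 D |
| Power, 40 per group, θ assumed 0.3: one-sided 0.05 | >99.9% | 55% |
| Same, two-sided 0.05 | >99.9% | 42% |

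The two columns are alternatives. The 5% false-claim rate at no effect and the fall in power from 55% to 42% cannot both apply.

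**The case against.** The strongest reply is that the quantile and the analysis agree. The design calculation uses 1.645 and the analysis tests one-sided at 0.05, so the coherent reading is a trial planned and analysed at one-sided 0.05 with one stray label. This largely stands: the trial was not sized at two-sided 0.05, and the word in the Sample size section is the odd one out. The nominal total error also stays at 5%; what differs is the share in the favoured direction. Even so, the article declares one error rate and applies another, and deleting the label would leave a one-sided 5% rule without a stated reason.

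Three stronger readings are tempting, and the document does not support them.
- A reader might infer that acupuncture's false-positive rate is simply doubled, or that a two-sided p of 0.08 would always win. That holds only for a test against zero. If the margin is tested, success needs about 0.293 D.
- A reader might take Table 2 as a third contradiction. Its wording describes change after treatment rather than the sidedness of a test, the row above it is directional (improvement), and neighbouring rows are equally loose.
- A reader might conclude that harm cannot be detected. The one-sided efficacy test cannot declare faster progression significant, but adverse events are recorded, compared between groups and analysed in a safety dataset.

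**Conclusion.** The point holds as a contradiction in the stated decision threshold. The false statement is the two-sided label in the Sample size section; the calculation and the analysis both use one-sided 0.05.

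Its size depends on something the article leaves open. Against zero, the error in acupuncture's favour is 5% rather than 2.5%, and moving to two-sided 0.05 costs almost no power. Against the margin, the false-claim rate at no effect is negligible under either rule, but a true two-sided level needs about 27% more per group, or leaves power near 42% instead of 55%.

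The error rates need no assumption beyond the choice of test. The power and sample-size figures rest on SD 0.25, 20% dropout and the assumed θ of 0.3; with the stated 3.0, the formula asks for one child per group under either rule.

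**What to change.** - State one rule in both sections. Preferred: two-sided 0.05, equivalently one-sided 0.025, with a 95% confidence interval for the between-group difference. Replace the one-sided sentence in Statistical analysis to match.
- Use the matching quantile, 1.96, in the Sample size section.
- Say in Statistical analysis whether the primary test is against zero or against the 0.2 margin.
- Restate the power that 100 children give under that rule, without enrolling more.
- Optional tidying: word the primary hypothesis in Table 2 as a between-group difference.

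The cost is wording in two sections and a recalculation. The real downside is a lower stated power if the margin is tested (about 42% instead of 55% under the assumed θ); against zero there is almost none. Keeping one-sided 0.05 and deleting the two-sided label would also remove the contradiction, but it keeps the 5% directional error and would need a stated reason. Trial status reports six participants recruited, and the amendments section already provides for notifying changes to the analytical method, so this can be settled before any analysis.

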[19] will also be utilized to obtain more objective and quantitative results. This trial aims to confirm the effectiveness and safety of acupuncture in the treatment of adolescent myopia.

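### The one-sided rule has no exception for safety and the adverse-event hypothesis is worded as improvement; read literally with Fisher's exact test, the comparison would not flag an excess of events with acupuncture

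*Protocol article*

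**What the plan says.** Four statements in the protocol article bear on the adverse-event comparison.

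- Background gives safety equal standing with efficacy: "This trial aims to confirm the effectiveness and safety of acupuncture in the treatment of adolescent myopia".
- Statistical analysis assigns the test framework: "Primary and secondary outcomes will be analyzed by the superiority test in accordance with the principle of intention-to-treat". It then names the safety dataset: "The indices of safety evaluation will be analyzed using the Save Set (SS) dataset". The next sentence sets the significance level for the study at α = 0.05 and adds that "the one-sided test will be used". Nothing exempts safety.
- In Table 2 the adverse-event row stands in the secondary block. Its hypothesis is "Improvement occurred", its measure is "Presence of drug-related adverse event [binary]", and its method begins "Chi-squared test or Fisher", that is, the chi-squared or Fisher's exact test.
- Harms lists the events of interest (haematoma, bleeding, local infection, fainting, severe pain) and commits to reporting them.

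Under Intervention, controls wear single-vision lenses and are not needled.

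**The concern.** A one-sided test spends its whole error rate in one tail. For efficacy that can be argued for. For adverse events the tail implied by one-sided, superiority and improvement taken together is the one in which acupuncture has fewer events. Most of the listed harms come from needling, and the control arm is not needled, so the realistic signal is an excess in the acupuncture arm. A test pointed the other way returns a p-value near 1 for exactly that result.

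The trial sets out to confirm safety in children aged seven to 12 who are needled partly on the face. If the planned comparison is run as literally written, a non-significant p-value could accompany a clear excess of events.

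This is separate from the level of alpha. Moving to one-sided 0.025 would leave the direction of the safety test unchanged.

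**Working it through.** **The plan's own figure.** There is none for safety: the protocol gives no event rate, margin or power for adverse events. Its one computed figure is the sample size for diopter (79, raised to 100). That section labels alpha two-sided but uses 1.645, the one-sided value. This is a separate matter and does not settle the present one.

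**Inputs.**
- 50 per arm, 1:1 (Study design; Randomization).
- α = 0.05, one-sided (Statistical analysis).
- Binary adverse-event outcome, chi-squared or Fisher's exact test (Table 2).
- Event counts and rates: assumed, for illustration only.

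**Which test applies.** Statistical analysis chooses between the two tests by theoretical frequency but states no cut-off. Under the conventional threshold of an expected count below 5 (an assumption), equal arms give an expected count per arm of total events ÷ 2. Fewer than 10 events in total would then go to Fisher's test: 7 events give 3.5 and 9 give 4.5, while 10 give exactly 5.0 and would not. The Discussion expects almost no side effects, so Fisher's test is the likely route.

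**Fisher's test.** Given k events in total, the number X in the acupuncture arm has P(X = x) = C(50, x)·C(50, k − x) / C(100, k).
- Towards fewer events with acupuncture: P(X ≤ observed). If all k events are in the acupuncture arm, this is 1 whatever k is.
- Towards more: P(X = k) = C(50, k) / C(100, k). With equal arms the two-sided value is twice this.
- k = 9: 2,505,433,700 / 1,902,231,808,400 = 0.0013; two-sided 0.0026.
- k = 7: 99,884,400 / 16,007,560,800 = 0.0062; two-sided 0.0125.

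**Chi-squared, uncorrected, 1 df.** For k v 0 with 50 per arm the statistic is 100k / (100 − k): 6.38 for k = 6, 7.53 for k = 7, 9.89 for k = 9.

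| Events of 50, acupuncture v control | Fisher, towards fewer | Fisher, two-sided | Chi-squared |
|---|---|---|---|
| 6 v 0 | 1.00 | 0.027 | 0.012 |
| 7 v 0 | 1.00 | 0.0125 | 0.006 |
| 9 v 0 | 1.00 | 0.0026 | 0.002 |
| 10 v 2 | 0.998 | 0.028 | 0.014 |
| 0 v 6 | 0.013 | 0.027 | 0.012 |

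The last row is the mirror image of the first. The literal test would declare 0 v 6 significant and give p = 1.00 for 6 v 0.

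**Chance of flagging an excess**, by full enumeration of two binomials at 50 per arm and α = 0.05:

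| True rates, acupuncture v control | Fisher, towards fewer | Fisher, two-sided | Chi-squared |
|---|---|---|---|
| 10% v 1% | 0% | 27% | 53% |
| 20% v 5% | 0% | 51% | 66% |
| 20% v 2% | 0% | 78% | 89% |

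The 0% column holds only if the test is Fisher's and the tail is the one that the wording implies. The chi-squared column shows that the other test named in the row would respond to an excess.

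**The case against.** A reader might infer that the safety test can only ever show benefit, and that the trial therefore has no power to detect harm. The document does not support that, for these reasons.

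- **No tail is fixed.** No sentence states the direction of the safety test. The Hypothesis column of Table 2 is loose: the diopter entry allows movement either way, the compliance row repeats its own name, and the improvement wording also stands against use of other drugs. It may well be template text. This stands, and it makes the directional reading an inference.
- **The rule may be meant for efficacy.** It sits in a paragraph that opens with the superiority test, and a one-sided rule has no meaning for some tests in Table 2, such as the multi-category comparison of race at baseline. This is a fair reading, but the sentence says that it covers the study, follows directly on the safety sentence, and makes no exception.
- **Chi-squared in its usual form has no direction** and would flag 9 v 0. This stands. The row then contains a test that does not obey the stated one-sided rule, so the text still needs reconciling. The expected-count threshold that sends rare events to Fisher's test is a convention and is not in the protocol.
- **Harm would be visible anyway.** Harms commits to reporting events, categorical data are described by proportions, and a Data Monitoring Committee is planned. This stands and limits the consequence to the test result.
- **Sidedness of safety tests may be left to an analysis plan.** That would answer a silence. Here the article states a rule and a hypothesis, and the point is to correct what is stated.

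**Conclusion.** The concern holds in a limited form. The one-sided rule is set for the study without a safety exception, and the adverse-event hypothesis is worded as improvement under outcomes assigned to a superiority test. Taken literally, and where Fisher's exact test is used, the planned comparison would not flag an excess of events with acupuncture: p = 1.00 against 0.0026 two-sided for 9/50 v 0/50, and 1.00 against 0.0125 for 7/50 v 0/50. Where chi-squared is used, the excess is flagged but the stated rule is not followed. Either way the passages do not fit together.

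The size rests on assumed event counts, on 50 analysed per arm, and on reading the hypothesis cell as the direction of the test. The defect affects the planned safety test. It does not affect the listing of events or the efficacy analysis. It should be corrected, because safety is a stated aim and the wording points away from the only likely signal.

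**What to change.** - In Statistical analysis, limit the one-sided rule to the superiority tests of the efficacy outcomes.
- In the same place, state that adverse events and eye and systemic symptoms are compared two-sided, preferably with the risk difference and its 95% interval. The interval is a recommendation: with few events it tells the reader more than a p-value.
- In the adverse-event row of Table 2, replace the hypothesis with one saying that the proportion with an event differs between groups.

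The cost is a sentence or two and one table cell. No extra data, participants or visits are needed. The change should be notified as a change of analytical method under Protocol amendments and confidentiality. Trial status reports six participants recruited, so it can be made well before analysis. The downside is that the safety result may look less favourable to acupuncture.

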**Table 2 Tab2:** **Variables, measures, and methods of analysis**

Variable/outcome	Hypothesis	Outcome measure	Methods of analysis
1) Primary	Intervention improved outcome from baseline to 7 days	Adherence% (>80%) [binary]	
Diopter	Diopter reduced or increased after treatment	Diopter [continuous]	t-test (rank-sum test) or repeated measurement
2) Secondary	Intervention improved outcome from baseline to 7 days	Adherence% (>80%) [binary]	
Visual acuity	Visual acuity did not increase or decrease after treatment	Visual acuity changes [continuous]	t-test (rank-sum test) or repeated measurement
Axial length	Axial length was not increased	Axial length changes [continuous]	t-test (rank-sum test) or repeated measurement
Lens thickness	Lens thickness was not increased	Lens thickness changes [continuous]	t-test (rank-sum test) or repeated measurement
Ciliary body thickness	Ciliary body thickness was not increased	Ciliary body thickness changes [continuous]	t-test (rank-sum test) or repeated measurement
Eye symptoms and systemic symptoms	No adverse symptoms	No adverse symptoms	Chi-squared test or Fisher’s exact test
Compliance	Compliance	Cure rate [binary]	Chi-squared test or Fisher’s exact test
Combination therapy/treatment	Improvement occurred	Whether other drugs were used during treatment [binary]	Chi-squared test or Fisher’s exact test
Adverse event	Improvement occurred	Presence of drug-related adverse event [binary]	Chi-squared test or Fisher’s exact test
3) Baseline analyses:		Adherence% (>80%) [continuous]	
Age		CRF [continuous]	t-test (rank-sum test)
Weight and height		CRF [continuous]	t-test (rank-sum test)
Female versus male		CRF [binary]	Chi-squared test or Fisher’s exact test
Race		CRF [more categories]	Chi-squared test or rank-sum test
Birth weight		CRF [continuous]	t-test (rank-sum test)
Preterm children		CRF [binary]	Chi-squared test or Fisher’s exact test
Parental myopia or not		CRF [binary]	Chi-squared test or Fisher’s exact test
Sibling myopia or not		CRF [binary]	Chi-squared test or Fisher’s exact test
Daily close reading time		CRF [continuous]	t-test (rank-sum test)
Outdoor time		CRF [continuous]	t-test (rank-sum test)
Eye exercises every day or not		CRF [binary]	Chi-squared test or Fisher’s exact test
Daily sleep time		CRF [continuous]	t-test (rank-sum test)
Room light conditions		CRF [binary]	Chi-squared test or Fisher’s exact test
Poor reading habits		CRF [more categories]	Chi-squared test or rank-sum test

CRF, case report form ; rank-sum test, Wilcoxon rank-sum test; t-test, Student’s t-test.

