## Background

Myopia is becoming increasingly common and has become a worldwide public health issue
[1]. In the United States and Europe, the incidence of myopia is 20% to 50%
[2]; in Asian countries, such as mainland China, Taiwan, Hong Kong, and Singapore, the incidence of myopia is 60 to 80%
[3–5]. Over the past 50 to 60 years, the incidence of myopia in East and Southeast Asian countries has rapidly increased. Approximately 80 to 90% of urban adolescents in these countries have myopia on graduating from high school
[1]. Myopia often occurs between six and eight years of age, develops rapidly between 13 and 16 years of age, and stabilizes after 16 years of age
[6]. Treatment of myopia in modern medicine is mainly optometric, and includes the use of spectacles (single-vision lenses (SVLs) and progressive addition lenses
[7] and contact lenses
[8, 9]. Refractive surgeries include laser-assisted *in situ* keratectomy, photorefractive keratectomy
[10–12], and posterior chamber phakic intraocular lenses
[13]. However, while the most commonly used treatment method (optometric) can increase the best corrected visual acuity, optometric methods are unable to improve the uncorrected visual acuity. Surgery can help eliminate the need for glasses, but may lead to complications, as indicated by long-term follow-up studies
[13, 14]. There is also an age limit for performing such surgery, and it is considered as the last treatment choice for teenagers.

Acupuncture is highly valued in traditional Chinese medicine, and enjoys a favorable history of more than 2,500 years. Acupuncture has helped millions of patients around the world, and has been shown to be effective in clinical treatment. In 1980, the World Health Organization recommended acupuncture as an effective alternative therapy
[15]. Previous studies have confirmed that acupuncture, ear pins, or ear massage can help treat mild myopia (<-3.0 D)
[16]. There are published reports on the use of acupuncture in the treatment of adolescent myopia, but most studies use visual acuity as the primary outcome measure. Indeed, visual acuity, as determined by eye examination, is easily influenced by many external factors. Therefore, we have designed a randomized controlled trial based on the physiology and pathology of myopia. In addition to using distance visual acuity, diopter, and axial length (AL)
[17] as indices of clinical observation, indices such as ciliary body thickness
[18] and lens thickness

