**Flow of participants.**

### Recruitment

This study will be conducted in the Department of Ophthalmology, Xinjiang Uygur Autonomous Region Institute of Traditional Chinese Medicine (Xinjiang Medical University Affiliated Hospital of Traditional Chinese Medicine, a grade III level A teaching hospital). Adolescents with mild-to-moderate myopia will be recruited from the 27th Elementary School near the Xinjiang Uygur Autonomous Region Institute of Traditional Chinese Medicine after an ophthalmologic examination. Inclusion criteria will be as follows: the result of retinoscopy is myopic refractive error; distance visual acuity can be corrected to normal using negative spherical or cylindrical lenses; near visual acuity and other visual functions must be normal; myopia diopter spherical lenses must be between -0.5 D and -6.00 D, and cylindrical lenses <1.5 D, as measured under cycloplegia; and adolescents must be between seven and 12 years of age. Exclusion criteria will be as follows: subjects with serious systemic diseases, such as cerebrovascular, liver, kidney, hematopoietic system, and psychiatric diseases; long-term use of other related drugs or treatments, which have not been terminated; diopter < -0.5 D, or combined with pathologic myopia-related fundus changes and/or significant visual function impairment; and the affected eyes have other diseases which affect the determination of acupuncture efficacy.

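### Table 2 words the primary diopter hypothesis in both directions, which conflicts with the one-sided between-group superiority test, and no section says which diopter change counts as improvement

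*Protocol article*

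**What the plan says.** The Diopter row of Table 2 gives the primary hypothesis as "Diopter reduced or increased after treatment". The header row of the same block reads "Intervention improved outcome from baseline to 7 days", and the identical sentence heads the secondary block.

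The Statistical analysis section, which refers the reader to Table 2 for detailed methods, says "Primary and secondary outcomes will be analyzed by the superiority test in accordance with the principle of intention-to-treat". It adds: "The significance level in this study will be set at α = 0.05, and the one-sided test will be used". It also says that the t-test or rank-sum test compares the groups.

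The Sample size section opens with "The inspection significance level α = 0.05 (two-sided) with a combined standard deviation (S) of 0.25" but then uses 1.645 and 0.845, which it says "are the bounds of the one-sided standard normal deviation". It sets a positive superiority boundary of 0.2 and a mean difference between the acupuncture and control groups of 3.0, without saying which arm is subtracted from which.

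Under Recruitment, eligibility is written in negative numbers: "myopia diopter spherical lenses must be between -0.5 D and -6.00 D".

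**The concern.** A one-sided test needs one favourable direction, fixed in advance on the scale of the outcome. The row that states the primary hypothesis names both directions. A continuous measurement always moves one way or the other, so the sentence cannot be false, and worsening meets it as readily as benefit.

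The sign of the outcome does not rescue it. Where myopia is written as a negative number, a reduced diopter can mean a smaller magnitude (less myopia) or a more negative value (more myopia). What is at stake is the error rate of the main test and whether a harmful difference could be reported as meeting the stated hypothesis.

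**Working it through.** **1. The row beside the planned test.**

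| Element | Table 2, primary block | Other sections |
|---|---|---|
| Direction | Both (Diopter row); improvement (header row) | One-sided superiority (Statistical analysis) |
| Comparison | After treatment, no comparator | Between groups (Statistical analysis) |
| Time point | None (Diopter row); 7 days (header row) | Months 1, 3 and 6 after the two treatment months (Primary outcome) |
| Variable | Diopter value | Not stated as value or change |

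Table 1 has diopter at baseline and at months 3, 5 and 8, that is 2 + 1, 2 + 3 and 2 + 6. The 7 days of the header row are not a visit at which diopter is measured. In the same table, axial length, lens thickness and ciliary body thickness are each listed as changes and each name one direction. The primary outcome does neither.

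**2. Can the diopter direction be recovered from the sample-size inputs?** The boundary and the mean difference are both positive, so benefit must be the positive direction. There are four possible codings:

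- Signed diopter, acupuncture minus control: positive means less myopia with acupuncture (benefit).
- Signed diopter, control minus acupuncture: positive means more myopia with acupuncture (harm).
- Magnitude, acupuncture minus control: positive means harm.
- Magnitude, control minus acupuncture: positive means benefit.

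Two codings fit a superiority test and two do not. The article does not say which is used.

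**3. Is a sign convention implied elsewhere?** Not consistently. The Recruitment range is negative. The Abstract, however, describes eligible spheres as <-6.00 D, and Recruitment excludes diopter < -0.5 D. Read as signed numbers, the first would select eyes more myopic than the eligible range and the second would exclude nearly every eligible child. Both work only as magnitudes. The cylinder limit carries a minus sign in the Abstract (-1.50 D) and none under Recruitment (1.5 D).

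**4. Size.** Take a one-sided test against zero at 0.05. With no difference between the arms, the upper tail is exceeded with probability 0.05 and the lower tail with probability 0.05. Accepting either as confirmation gives 0.05 + 0.05 = 0.10. At a two-sided 0.05, the total would be 0.025 + 0.025 = 0.05.

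The figure depends on testing against zero. Suppose instead that a difference beyond 0.2 were required in each direction. With 50 per arm and S = 0.25, the standard error is 0.25 × √(2/50) = 0.05. At a true difference of 0.2, the opposite boundary of -0.2 lies 0.4/0.05 = 8 standard errors away, so the second tail adds practically nothing and the rate stays at about 5%.

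**5. The plan's own sample size.** The usual formula is n per arm = 2S²(u₁₋α + u₁₋β)²/(θ − δ)². With the stated inputs this is 2 × 0.25² × (1.645 + 0.845)²/(3.0 − 0.2)² = 0.775/7.84 = 0.10, not 79. If the 3.0 is assumed to be a slip for 0.3, the result is 0.775/0.1² = 77.5, so 78 per arm. That is near 79, but only as a per-arm number; the two-sided version gives 99. The calculation is thus directional in its quantile, but it does not reproduce from its stated inputs and cannot supply the missing sign. The mismatch in n is a separate matter.

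**The case against.** The strongest reply is that the direction is not really absent. A superiority test, a positive boundary and the header row's reference to improvement all point to acupuncture being better than control, and in a myopia treatment trial improvement most naturally means less myopia. An article may leave sign coding to a fuller document. This stands as far as it goes: it would be wrong to say that the one-sided test has no direction at all. What is missing is the direction for diopter. The Diopter row does not merely omit it; it states a hypothesis that contradicts the test.

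One could also read the row as an ordinary two-sided alternative, in line with the two-sided label under Sample size. That would be coherent with a two-sided test, but the Statistical analysis section specifies a one-sided one.

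A reader might infer something stronger: that natural progression in growing children would confirm the hypothesis in both arms without any treatment effect. It would satisfy the sentence in the row, but the planned test compares groups, and equal progression in both arms produces no expected difference between them. Nothing in the article makes a within-arm test the basis of the conclusion, and it gives no progression rate for the enrolled ages.

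Nor does the article say that the tail will be chosen after the data are seen. The 10% describes what the row permits, not a declared intention.

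**Conclusion.** The point holds in this form. The Diopter row of Table 2 is two-directional and has no comparator. It conflicts with the one-sided between-group superiority test at 0.05 and with the improvement stated in its own header row, and no section says which diopter change is improvement.

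The size is a false-positive rate of 10% instead of 5%, on two assumptions: either direction is accepted at the one-sided critical value, and the test is against zero. A test carried out strictly in the direction of benefit keeps its 5%. The documents do not support a claim that the trial would succeed on natural progression alone. The defect is in a stated rule for the only primary outcome and should be corrected.

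**What to change.** Replace the Diopter row with one directional between-arm hypothesis. For example: let D be the mean change from baseline in signed cycloplegic diopter (negative = myopic) in the acupuncture arm minus that in the control arm, so that a greater D means less myopic shift with acupuncture; the alternative is that D exceeds the stated bound.

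Alongside it:

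- Choose the bound. Either test against the 0.2 boundary of the Sample size section, or state that the test is against zero and reconcile that section with it.
- Name one primary time point from the visits already planned, and remove the 7-day wording from the header row.
- State that a difference in the opposite direction does not support efficacy.
- Use one sign convention in the Abstract, Recruitment and Table 2, and one label for sidedness in Sample size and Statistical analysis.

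The cost is a table row, a few sentences and the notification that the article already requires for a major change to outcomes or analytical method. No further measurements are needed. Whether the sample size must change depends on the bound chosen, and that calculation needs reconciling in any case. Trial status reports six participants recruited, so the change can still be made early.
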